### Intervention

#### Intervention group

In the intervention period, the participating household’s main cook in the intervention group will install the smart salt checker in their households, and receive the personalised reports and health education through the salt-limiting WeChat mini programme monthly. Personalised reports will mainly contain the daily added salt intake of each household member, the adverse impact of excessive salt consumption and the salt-limiting suggestions. The health education includes salt-limiting guidance and targeted health articles. The salt-limiting guidance will be provided by professional nutrition experts through the salt-limiting WeChat mini programme. People from the target population can select the intervention content depending on their specific situations and interests. The participating household’s main cook can propose questions and ask for suggestions from the nutrition experts in real time through the WeChat mini programme. The intervention period will last for 6 months. Through the personalised reports and health education, we seek to provide the participating household’s main cook with useful and effective guidance on two aspects:
Provide the daily added salt intake of each household member.Convey knowledge and suggestions on the negative effects of excessive salt consumption and ways to limit salt consumption and maintain healthy behaviour.

#### Control group

The household’s main cook in the control group will have access to the smart salt checker with only the weighing function.

#### Qualitative interview of participating household cooks

After 6 months of intervention, a semi-structured in-depth interview (20–30 minutes each) will be conducted among a sample household main cooks from the intervention group. The selection of subjects for the interview will follow the dynamic sampling and information saturation principles until no new useful information can be collected by adding new subjects. Several open-ended questions will measure the household’s main cook’s satisfaction of the system (i.e. ‘Would you like to recommend the system to friends who also want to reduce their salt consumption?’), the effect of the system on salt reduction (i.e. ‘What are the benefits of using the system?’), suggestions on optimisation and intelligence of interface (i.e. ‘What are the limitations of using the system?’) and other aspects to conduct a primary evaluation of the monitoring system. A sample of those who do not continue using the system will be interviewed and the reasons documented. Figure 3 shows the schedule of enrolment, assessment and intervention.

**Fig. 3 Fig3:**
[figure not shown]
Schedule of surveys

#### Primary outcomes

Daily added salt intake of each household member, assessed at baseline, 3 and 6 months.Salt consumption-related KAP of the household’s main cook, assessed at baseline, 3 and 6 months.

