#### Stage 2: Evaluation of the effectiveness of SALTCHECKER

To evaluate the effectiveness of SALTCHECKER, we will (1) assess the time trend of salt intake change during the study period and (2) compare the individual salt intake of the household member and the salt consumption-related KAP of the household’s main cook between the intervention group and the control group at baseline, 3 and 6 months.

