### Study sample

To calculate sample size, the following formula will be used:

$$ N=\frac{{\left({U}_{\alpha }+{U}_{\beta}\right)}^2\times 2P\left(1-P\right)}{{\left({P}_1-{P}_2\right)}^2} $$

where α = 0.05, β = 0.1, and then U_0.05_ = 1.96, U_0.1_ = 1.28. According to a previous study in China, the proportion of daily per capita salt consumption ≤6 g was 37.91% and the proportion increased to 45.91% after using salt-control spoons in participating households [16]. Thus, in this study, the increase in low salt consumption (≤6 g/d) with SALTCHECKER from about 38% (*P*_*1*_) to some 46% (*P*_*2*_), *P* = (*P*_1_ + *P*_2_)/2 = 0.42 was assumed. The sample size is calculated to be 799 cases. According to some similar salt-limiting trials, the dropout rate was 0.5–5% [18, 40–42]. And sampling error and invalid questionnaires may be 10–15%. Therefore, it was assumed 10–20% should be added on the basis of the estimated sample size, so 879–959 participants will be needed. The data of the tabulation on the 2010 population census of the People’s Republic of China (No. 1) indicated that the average household size in Chongqing is 2.70 (person/household) [43]. Therefore, 300 households’ main cooks in each of the intervention group and control group will be investigated in this study.

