### Procedure

A baseline survey will obtain the household demographic information and the salt consumption-related KAP of the household’s main cook. In the test period, the household’s main cook in the intervention group will use the smart salt checker and the salt-limiting WeChat mini programme, while the household’s main cook in the control group will use the smart salt checker with only the weighing function. The data of the daily added salt intake of each household member will be automatically calculated using SALTCHECKER. And the salt consumption-related KAP of the household’s main cook will be assessed at the beginning of the test (i.e. at baseline), the third month and the sixth month after the test. Finally, the effect of the household added salt monitoring system will be evaluated by changes in daily added salt intake of each household member and the salt consumption-related KAP of the household’s main cook. The technological roadmap is shown in Fig. 2.

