### Analysis strategy

Statistical analyses will be conducted using SPSS version 22.0 (IBM Corp, Armonk, NY, USA). Descriptive statistics will be calculated for all the variables under examination. The counting data will be described by frequency and percentile, and the metrological data description will use mean, standard deviation and median. The demographic characteristics of the household members (e.g. age, gender, ethnicity, occupation, marital status, education level, height, weight and health status) will be analysed to examine the influencing factors of the household salt monitoring system by using multivariate regression analysis. Linear mixed models, generalized estimating equations (GEE) or t-test will be used to examine the predictors of added salt intake of each household member and salt consumption-related KAP of the household’s main cook and the moderators, mediators of the intervention effects. Correlation analysis will be used to test the link between the score of salt consumption-related KAP and daily added salt intake of each household member. Meanwhile, we will analyse the time trends of the daily added salt intake of each household member during the study period. The level of significance will be set at < 0.05. For the qualitative data analysis, the audio recordings will be transcribed verbatim by trained transcribers. Content analysis of the qualitative information gathered will be done using MAXqda. In addition, if there is enough data acquired about blood pressure, analysis of the impact of the system on blood pressure will be considered.

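### Two unranked primary outcomes at two visits share one 0.05 level, while the only power calculation is for a ≤6 g/d proportion that is not a listed outcome

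*Protocol article*

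**What the plan says.** *Primary outcomes* in the protocol article has two entries: "Daily added salt intake of each household member, assessed at baseline, 3 and 6 months" and "Salt consumption-related KAP of the household’s main cook, assessed at baseline, 3 and 6 months". Neither is ranked above the other, and neither follow-up visit is called primary.

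*Study sample* sizes the trial on something else, "the increase in low salt consumption", meaning the proportion at or below 6 g/d rising from about 38% to some 46%. The inputs are "α = 0.05, β = 0.1, and then U_0.05_ = 1.96, U_0.1_ = 1.28", and the result is 799. The section gives no mean difference or standard deviation for added salt or for the KAP score. The published figures behind 38% and 46% concern daily per capita salt consumption, whereas the listed outcome is added salt only.

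*Analysis strategy* states "The level of significance will be set at < 0.05". It offers linear mixed models, GEE or a t-test, and describes no analysis of the ≤6 g/d proportion.

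The effect is described in several ways. *Stage 2* will "assess the time trend of salt intake change during the study period" and will also compare the groups at baseline, 3 and 6 months. *Procedure* says "the effect of the household added salt monitoring system will be evaluated by changes in daily added salt intake of each household member", and likewise for KAP. The *Discussion* expects lower salt and higher KAP than in the control group, and also a falling salt trend inside the intervention group.

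**The concern.** A power statement and a significance level are useful only if they belong to the test that will decide the trial. Here they belong to a binary comparison that the outcome and analysis sections never mention. The outcomes that are listed have no stated effect size, variability or power.

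The open choice of visit matters as well. The *Discussion* expects a larger effect from baseline to 3 months than from baseline to 6 months. With neither outcome nor visit fixed, salt or KAP at 3 or 6 months could each be presented as the primary result, and the more favourable one could be chosen after the data are seen.

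The time-trend wording adds a further route to a positive statement. Monitoring runs from April to September (*Trial status*). A fall within the intervention group alone would mix the intervention with season and with reaction to being weighed and observed. Only the comparison with the control group draws on the randomisation.

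**Working it through.** **1. Reproduce the protocol's figure.** Inputs from *Study sample*: U values 1.96 and 1.28, P1 = 0.38, P2 = 0.46, P = 0.42.

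- 2P(1 − P)/(P1 − P2)² = 2 × 0.42 × 0.58 / 0.08² = 76.125
- N = (1.96 + 1.28)² × 76.125 = 10.4976 × 76.125 = 799.1

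The 799 is reproduced. The formula gives a size per group, for one two-sided test of one proportion.

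**2. Match the endpoint across sections.**

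| Section | Quantity |
|---|---|
| *Study sample* | Proportion at ≤6 g/d (binary) |
| *Primary outcomes* | Added salt per member; KAP of the cook |
| *Analysis strategy* | Added salt and KAP; no ≤6 g/d proportion |

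The powered quantity appears only in the first row.

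**3. Count the primary tests.** Two outcomes × two follow-up visits = 4 between-arm tests. The baseline comparison is not an efficacy test and is not counted.

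**4. Family-wise error if each is judged at 0.05 and there is no true effect.**

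- Two outcomes at one visit, independent: 1 − 0.95² = 9.75%
- Four tests, independent: 1 − 0.95⁴ = 18.5%
- Four tests with an assumed equal pairwise correlation (simulated, 500,000 draws): 0.3 gives 17.4%, 0.5 gives 15.5%, 0.8 gives 11.4%

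The protocol gives no correlations. Visits 3 months apart on the same outcome will be positively correlated, so 18.5% is a ceiling.

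**5. What controlling the error would cost, on the protocol's own effect.** With the formula from step 1 and a Bonferroni split:

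- Two tests, alpha 0.025: (2.2414 + 1.28)² × 76.125 ≈ 944 per group
- Four tests, alpha 0.0125: (2.4977 + 1.28)² × 76.125 ≈ 1,086 per group

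With 799 per group held fixed, power is the normal probability below √(799/76.125) − z = 3.240 − z. For z = 1.96, 2.2414 and 2.4977 this is 90%, 84% and 77%. These figures treat household members as independent.

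**6. Can power for the listed outcomes be derived?** Not from the document, because no difference or SD is given. Two illustrations show what is missing:

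- KAP, 300 cooks per group with no losses, 90% power: the detectable difference is (1.96 + 1.28) × √(2/300) = 0.26 SD at alpha 0.05, and (2.4977 + 1.28) × √(2/300) = 0.31 SD at 0.0125. Whether that is a plausible effect cannot be judged without an SD.
- Salt, if intake were normal with equal SD in both arms: moving from 38% to 46% below a cut-off is a shift of 0.3055 − 0.1004 = 0.205 SD. A comparison of means would then need 2 × 3.24² / 0.205² ≈ 500 independent persons per group, fewer than 799.

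The second illustration shows that the mismatch need not mean low power.

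**The case against.** The strongest reply is that a statistical analysis plan may exist. Multiplicity procedures and model covariates are commonly left to it, and a mixed model or GEE could give one joint test per outcome. One general significance level does not say that four separate tests will each count as success. This stands as a limit: testing each at 0.05 is a reading of the text, not a statement in it. It does not remove the mismatch, because the sample-size endpoint and the outcome list are both fixed in this article and disagree.

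Several stronger readings are tempting and are not supported:

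- *The trial is underpowered.* Step 6 shows that a continuous salt outcome could need fewer people than the dichotomy.
- *The false-positive rate is 18.5%.* That is the independence figure; plausible correlations bring it down.
- *Both outcomes are tested as values, changes and trends.* Trends are planned for salt only.
- *The falling trend in the intervention group is the planned test.* It appears as an expectation in the *Discussion*, and *Stage 2* does specify a between-group comparison.
- *Regression to the mean is built in.* *Recruitment* does not select on high salt intake, so the whole intervention arm has no such mechanism.
- *Baseline is ignored in the analysis.* That would be inferred from silence, and the named models can include it.

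The study is also called a pilot (*Design*) that will inform a larger trial. This tempers the weight of the point, but the article states an effectiveness aim and calculates 90% power.

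**Conclusion.** The point holds in this form. Two primary outcomes at two visits are unranked under one general 0.05 level, and the only alpha and power calculation concerns a proportion that is neither listed as an outcome nor given an analysis. Power for added salt and for KAP is undocumented, in either direction.

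The size is a family-wise error of at most 18.5%, more plausibly 11–17% under assumed correlations of 0.8–0.3, if all four between-arm tests can support a positive claim. Splitting alpha would raise the protocol's own 799 per group to about 944 (two tests) or 1,086 (four tests).

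A reader might also infer that adjusting for baseline salt is a free gain in precision. The article does not secure that. *Baseline survey* lists added salt and *Randomization and blinding* places allocation after that survey. But *Procedure* mentions only demographics and KAP at baseline, and the intake formula averages over 30 days. *Intervention* has the device installed during the 6-month intervention period, and *Trial status* monitors salt for exactly 6 months. Whether salt is measured before randomisation is therefore unclear.

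This should be corrected before the data are analysed.

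**What to change.** 1. Name one primary between-arm contrast at one visit. Added salt at 6 months is one option. The ≤6 g/d proportion is another, if the existing calculation is to be kept; it must then be listed as the outcome and given an analysis.
2. Make the other visit and KAP secondary in a stated fixed order. If both outcomes are to stay primary, split alpha and state the split.
3. Restate the power in *Study sample* for the chosen contrast, with its own assumed difference and, for a continuous outcome, its SD.
4. Base effectiveness claims on the between-arm (group-by-time) comparison. Treat a trend within the intervention arm as description.
5. Adjust for baseline KAP in the KAP analysis. Adjust for baseline salt only if it is measured before randomisation. *Procedure*, *Baseline survey*, *Randomization and blinding*, *Intervention* and *Trial status* must first be reconciled on when that measurement is taken.

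Items 1, 2 and 4 change text only. Item 3 needs a difference and SD from outside this document, and the resulting power may be less favourable than 90%. Item 5 may need more than wording if no pre-randomisation salt measurement exists. Under the fixed order, one outcome loses primary status.

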### Quality control

#### Online questionnaire survey

The participating household’s main cook can log on to the WeChat mini programme with the password set by themselves to complete the online questionnaires. The system will automatically send the electronic KAP questionnaire to the participants at baseline, 3 and 6 months. If the participant does not complete the questionnaire within 1 week, a text message will be sent or call made to remind him or her. A branched algorithmic structure will be used to enhance the confidentiality and accuracy of responses and reduce the risk of exposing sensitive information.

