#### Questionnaire survey

A self-administered questionnaire will be designed based on the local and international literature to assess the salt consumption-related KAP of the household’s main cook. The questionnaire will be sent to the household’s main cook through the salt-limiting WeChat mini programme. After the pre-investigation, the reliability and validity of the questionnaire will be tested. The questionnaire will include the following three parts:
Knowledge of salt consumption, such as the daily recommended intake of salt, high-salt diet hazards, recognition of seasonings and food with high sodium, etc. The knowledge of salt consumption is measured (0 = no, 1 = yes, 0 = do not know), and some items require reverse coding.The attitude of salt consumption, such as the attitude to salt-limiting or low-salt diets, awareness and intention of choosing a low-salt diet, etc. will be assessed using the 5-point Likert scale (1 = strongly disagree to 5 = strongly agree) questions.The practice of salt consumption, such as the use of low-sodium salt, proper use of salt-limiting spoons, selection of low-salt food, requiring low-salt food in restaurants, selection of food based on the nutrient list, etc. will be measured using the 5-point Likert scale (1 = strongly disagree to 5 = strongly agree) questions.

A total score will be calculated for the above items, and a high score will represent a high KAP.

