There are also four main limiting factors in this study. First, the method of estimating the added salt intake of each household member may not be accurate. Although we will take measures to reduce the salt consumption measurement error, we cannot ensure the salt used for cooking or at the table is taken from the salt checker container only. In addition, the salt intake may be from at-home and out-of-home sources, and the average prevalence of food away from home consumption increased from 9.40% to 13.95% between 2004 and 2011 in China [49]. Although at present, the SALTCHECKER can only measure the added salt consumption at home, we will use the salt-limiting WeChat mini programme to obtain information on participants’ dietary behaviours, such as the frequency of eating out, the places to eat, and the number of meals per day. We also hope to have a smarter and more accurate way to monitor salt intake from other sources such as out-of-home eating, ultra-processed foods and condiments containing sodium in the future. Second, we cannot ensure that all household main cooks will persist in receiving the intervention on the salt-limiting WeChat mini programme, which may hinder the intervention effects. To address this limitation, we will send prompting text messages to the participating household’s main cook at a fixed time weekly and set a daily punch-in reminder function in the WeChat mini programme. Besides, we will provide some reward (e.g. a salt spoon with a scale, a sphygmomanometer and a smart watch) to promote adherence to the daily use of the system for the participants. All relevant data can be entered into the registry database in the WeChat mini programme flexibly and dynamically, and which the participants can view their data at any time with the Internet. Third, the salt-limiting effects may be insignificant because the planned intervention time is 6 months. Although we found that 6 months of salt-limiting intervention could have an effect in a previous study [45], we hope the intervention time will be extended and the long-term salt-limiting effects will be reflected in further research. Fourth, this study will be conducted in Chongqing, China, where the dietary habits are different from those in other places. This setting may limit generalisability, but the feasibility of the findings will inform the development of a larger effectiveness trial.

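### The only route described for the KAP primary outcome is the mini programme that also delivers the intervention, so non-response may relate to adherence and differ by arm, with uncertain direction of bias

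*Protocol article*

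**What the plan says.** The Primary outcomes section of the protocol article lists "Salt consumption-related KAP of the household’s main cook, assessed at baseline, 3 and 6 months". Two sections describe how it is collected. Questionnaire survey states "The questionnaire will be sent to the household’s main cook through the salt-limiting WeChat mini programme". Online questionnaire survey, under Quality control, states that the cook "can log on to the WeChat mini programme with the password set by themselves to complete the online questionnaires", that "The system will automatically send the electronic KAP questionnaire to the participants at baseline, 3 and 6 months", and then: "If the participant does not complete the questionnaire within 1 week, a text message will be sent or call made to remind him or her". No other way of answering is described.

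The Intervention group section delivers the monthly personalised reports, the health education and the exchange with nutrition experts through this same mini programme. The Discussion says it cannot be guaranteed that every main cook will "persist in receiving the intervention on the salt-limiting WeChat mini programme, which may hinder the intervention effects". It plans weekly text prompts, a daily reminder in the programme and rewards in response. For households that give up, the section on qualitative interviews says "A sample of those who do not continue using the system will be interviewed and the reasons documented".

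On the control arm the article gives two pictures. The Abstract, Procedure and Control group sections describe a checker that only weighs, and the Abstract names the mini programme as a component of the experimental arm. Recruitment, however, makes willingness to have the mini programme on the phone an entry criterion for every cook, and both questionnaire sections address all participants without distinguishing arms.

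**The concern.** A primary outcome is collected on the platform that is itself a main component of the tested intervention, and the follow-up of non-responders ends at a reminder to return to that platform. An intervention cook who has lost interest in the programme has to go back to it to supply the 3- and 6-month scores. It is reasonable to expect that such cooks answer less often and that they differ in KAP from those who stay. The planned contact with people who stop is qualitative, covers only a sample, and gives no KAP score to fill the gap.

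Control cooks have no reports or education to give up, so their reasons for not answering are different. Missing scores may then differ between arms both in number and in the kind of cook who is missing, and the comparison of responders need not equal the randomised comparison. The article presents the study as real-world evidence, in which households that do not persist belong to the answer. A score not collected at 3 or 6 months cannot be recovered later.

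**Working it through.** **The plan's own figures.** The article gives no KAP standard deviation, no KAP effect and no expected non-response by arm. Its only sample size (Study sample) concerns the proportion at or below 6 g/d: (1.96 + 1.28)² × 2 × 0.42 × 0.58 / 0.08² = 10.4976 × 0.4872 / 0.0064 = 799.1, which reproduces the stated 799. The same section gives dropout of 0.5–5% in similar trials and a separate 10–15% for sampling error and invalid questionnaires. Neither figure is split by arm, and neither is a log-on rate.

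**Inputs.** From the article: 300 cooks per arm (Randomization and blinding) and α = 0.05 with critical value 1.96 (Study sample). Assumed: KAP in SD units with SD 1, no true effect, all 300 controls answering, a share m of intervention cooks missing, and missing cooks g SD below responders, with g from 0.2 to 0.5.

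**Formulas.** The responders' mean exceeds the mean of the whole arm by m × g, so bias = m × g. SE = √(1/(300(1 − m)) + 1/300). Rejection rate = P(Z > 1.96 − bias/SE) + P(Z < −1.96 − bias/SE).

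**One case in full** (m = 20%, g = 0.5): bias = 0.2 × 0.5 = 0.10 SD; SE = √(1/240 + 1/300) = √0.0075 = 0.0866 SD; bias/SE = 1.155; P(Z > 0.805) + P(Z < −3.115) = 0.210 + 0.001 = 0.211.

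| m | Intervention responders | SE (SD) | Bias, g = 0.2 to 0.5 (SD) | Rejection rate |
|---|---|---|---|---|
| 5% | 285 | 0.083 | 0.010 to 0.025 | 5.2% to 6.1% |
| 10% | 270 | 0.084 | 0.020 to 0.050 | 5.7% to 9.2% |
| 20% | 240 | 0.087 | 0.040 to 0.100 | 7.5% to 21.1% |

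**Precision.** The difference detectable with 90% power is (1.96 + 1.28) × SE. With nobody missing it is 3.24 × 0.0816 = 0.265 SD; at m = 20% it is 3.24 × 0.0866 = 0.281 SD. The loss of precision is small; the issue is bias.

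**Direction.** If controls are missing too, bias = m_I × g_I − m_C × g_C, where I is the intervention arm and C the control arm. With g = 0.5 in both arms and equal non-response it is zero. With m_I = 10% and m_C = 20% it is 0.05 − 0.10 = −0.05 SD, against the intervention. The table's positive sign comes from the assumption that controls are complete.

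**The case against.** The strongest reply is that losing interest in the reports is not the same as being unable to answer a questionnaire at 3 and 6 months. The Background notes that a mini programme needs no installing or uninstalling, so a lapsed cook keeps access, and the text or call after 1 week arrives outside the programme. A cook who then answers is a non-adherer with an outcome. This stands. A reader might infer that the KAP result describes adherers only, or that stopping the intervention and losing the outcome are one event. The documents do not support that: the result describes questionnaire responders, whose make-up may depend on adherence.

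A reader might also infer that the effect is bound to be inflated, adherers in one arm being set against everyone in the other. This is not supported either. Control cooks face the same log-on and have less reason to open the programme, so their non-response could be equal or higher.

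The planned prompts and rewards should reduce stopping. At 5%, the top of the quoted dropout range, the rejection rate stays near nominal. Since baseline KAP is measured before randomisation, adjustment for it or a mixed model could remove part of the bias. These points limit the size. They do not remove the link between outcome collection and the intervention platform.

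Finally, a condensed article may omit back-up routes. That is fair for retention rules, for analysis as randomised and for missing-data methods, none of which is counted here. The collection rule is different: the article describes it in two sections, including the step for non-responders, and that step is only a reminder.

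**Conclusion.** The point holds in limited form. KAP collection shares its platform with the intervention, no other route is described, and non-response leads only to a reminder. Non-response in the intervention arm is therefore likely to be related to giving up the programme. The article also does not reconcile a control arm described without the mini programme with a questionnaire that needs it. Missing data may differ by arm, and the direction of the resulting bias is uncertain.

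The size depends on non-response by arm, which the article does not give. Under the stated assumptions it is negligible to small at 5% missing, modest at 10%, and material at 20% only if missing cooks score well below responders. The 21% rejection rate is close to a worst case, since it needs 20% missing in one arm, a gap of 0.5 SD, complete controls and no baseline adjustment. This is a worthwhile and inexpensive improvement to the collection rule. It does not show that the KAP comparison is invalid.

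**What to change.** In Online questionnaire survey, extend the step for non-responders. For any cook in either arm who has not answered within 1 week, the reminder text should carry a link to the same KAP items, self-completed and working outside the mini programme. The items should be asked by telephone only as a last resort. Record the mode of each answer.

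Reconcile the Abstract, Procedure and Control group sections with Recruitment, Questionnaire survey and Online questionnaire survey: state whether control cooks have access to the mini programme, to which functions, and how they receive and answer the questionnaire.

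The cost is small, because the reminder texts and calls are already planned; a plain survey form has to be set up. The downside is a mixed mode for a minority of answers. Attitude and practice items read out by staff invite socially desirable replies, and if that mode fell mostly on lapsed cooks in one arm, recording it would not remove the difference. Keeping the back-up route self-administered keeps this small.
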